## Abstract

**Background:**

Health service programmes frequently encounter challenges with patient adherence to care. A promising, low-risk approach to address this issue is providing patients with targeted information about the importance of adherence. In the Vision Impact Project (VIP), an eye health screening programme in Kenya, the adherence rate to attending triage clinics after referral is around 50%. To improve this rate, this trial will test the effectiveness of delivering relevant information to patients at the point of referral along with reminder messages.

**Methods:**

A pragmatic, Bayesian adaptive trial will be conducted within the VIP programme to assess the effectiveness of providing enhanced information compared to standard care. Weekly interim analyses will monitor adherence rates to referral appointments following positive vision impairment screenings. Participants will be randomized equally into intervention and control groups. The trial will stop if interim findings indicate either efficacy of one arm over the other, or futility that the two arms are performing equally.

**Discussion:**

This paper presents the statistical analysis plan for a pragmatic adaptive trial aimed at improving adherence in an eye screening programme in Kenya. This statistical analysis plan expands on the design and analysis plan detailed in the study protocol and documents decision rules to avoid post hoc decision-making.

**Trial registration:**

ISRCTN 11329596, Registered on 02 February 2024,
https://doi.org/10.1186/ISRCTN11329596

## Introduction

### Background and rationale

Health service programmes often face challenges in improving patient adherence, particularly in screening initiatives designed to identify and connect patients with care. This issue is evident in vision impairment (VI) screening, where timely access to care is crucial for enhancing quality of life and preventing avoidable complications such as blindness. Peek Vision (
https://peekvision.org), a social enterprise, aims to address the global burden of VI by providing eye screening and patient management tools that facilitate referrals to local healthcare systems. To date, Peek Vision has screened over eight million people worldwide, identifying about 1.6 million in need of eye care. Despite the efforts, internal data shows that adherence rates are around 50%, revealing a gap in connecting patients to care.

In the Vision Impairment Project (VIP) based in Kenya, which employs Peek Vision’s screening platform, similar trends have been observed. Young adults aged 18–44 show particularly low adherence rates around 30%, highlighting the need for targeted interventions for this group. Interviews and surveys with these young adults have identified key barriers and potential solutions to improve adherence
^
1
^. One promising strategy is to provide information about the importance of care to increase awareness and encourage health-seeking behaviour.

These service modifications are low-risk and expected to yield modest improvements on attendance. Traditional, fixed-duration trials to test such incremental changes could be resource-intensive and time-consuming. As an alternative, we will conduct a pragmatic adaptive trial within the VIP programme, leveraging accumulating data and early stopping rules. The trial will assess whether providing additional information at the point of referral and via SMS reminders can enhance adherence and increase the proportion of people attending triage clinics. The trial setting, eligibility criteria, intervention definitions, and outcomes measurements have been described in detail in the study protocol
^
2
^. This paper expands on the protocol by providing a detailed statistical analysis plan.

### Objectives

To evaluate whether providing information about the importance of care increases the attendance rates in patients compared to those receiving standard care

### Trial design

This study is a pragmatic, Bayesian adaptive two-arm parallel trial embedded within the VIP programme. This trial was registered with ISRCTN on 2 Feb 2024 (registration number: ISRCTN11329596; DOI:
https://doi.org/10.1186/ISRCTN11329596).

## Trial objectives and design

The detailed methodology of the trial, including eligibility criteria, methods of enrolment, and provision of the intervention, has been described in the study protocol
^
2
^.

### Study setting

This is a pragmatic trial embedded within the VIP programme operating in Meru, Kenya. It integrates the eye screening tool developed by Peek Vision, with data being managed on its patient management software.

### Eligibility criteria

This study will enrol adults (>18 years) who access the VIP programme at their local clinics, have been screened positive for vision impairment, and have consented to participate in the trial.

### Interventions

Participants will be randomly assigned to one of two groups in equal numbers. Both groups will be read a script from a screener at the point of referral and receive reminder SMS messages. The control group will receive standard referral counselling and two standard reminder SMS messages, which will include the location and date of the appointment. The intervention group will receive enhanced referral counselling and three reminder SMS messages, including an extra reminder message on the day of the appointment. Both the scripts and SMS messages received by the intervention group will include additional information that emphasizes the importance of eye care and the benefits of attending the referral. This trial aims to determine whether providing relevant information – through counselling, enhanced reminder messages, and increased message frequency – improves attendance rates compared to standard care.

### Outcomes

The programme will enrol all eligible adult participants. But the primary outcome will focus on the proportion of attendance in adults aged 18–44 years, who were identified in the formative research as the group less likely to attend appointments. Successful outcome will be defined as attending the scheduled appointment or within 14 days of the appointment date. A secondary outcome will measure overall attendance rates within 14 days of the appointment among all enrolled adults.

## Statistical methods

This trial design was conceptualised with two main objectives: to determine which of the two programmatic options to pursue, and to achieve this without necessitating an excessively large sample size, even in the case of only marginal differences between the arms. To meet these objectives, we will employ an adaptive trial approach, enabling real-time assessment of accumulating data throughout the trial. By comparing the results of interim analyses against prespecified stopping rules, we will potentially end the trial early if sufficient evidence is accrued. As this is an adaptive trial, participants will continue to be enrolled until one of the stopping criteria is met. While a target sample size is not defined, the trial will proceed for a maximum duration of one year if neither stopping rule is triggered.

### Interim analysis

Once the trial begins, interim analyses will be conducted every 7 days, with an average of about 300 adults aged 18–44 enrolled each cycle. The first interim analysis will take place after allowing a 14-day window for participants enrolled during the initial 7 days of the trial to attend their appointment on the scheduled date or within 14 days thereafter.

Bayesian methods will be used to analyse attendance in each arm. At each interim analysis, the proportion of attendees in each arm will be described using a binomial distribution of the outcome probability. This data will be combined with prespecified prior distributions through 10,000 Monte Carlo simulations to generate posterior distributions of the outcome proportions and the effect difference between the arms. These posterior distributions will be compared to predefined stopping rules to determine whether the trial should continue or stop. The decision to stop the trial will be solely based on the primary outcome, focusing on young adults aged 18–44.

We will use a uniform prior for the outcome probability of the control arm, specified as
*logit(p) ~ norm(0, 0.3)*, reflecting variability between 0 and 1
^
3
^. We will also use a neutral prior for the effect difference between the two arms, with an odds ratio of 1.0 and a 95% credible interval (95% CI) ranging from 1/30 to 30. This neutral prior allows for detection of a wide range of effect differences and ensures that the posterior distribution is primarily driven by trial data rather than specified prior beliefs
^
4
^, enhancing the generalizability of the results across various settings.

### Stopping rules

During the trial design phase, two sets of stopping rules were established to determine when to stop the trial based on either efficacy or futility criteria. First, the trial will stop for efficacy if there is evidence that one arm is more effective than the other, indicated by an effect difference greater than 0%. The stopping rule for efficacy will be met if the posterior probability of an effect difference exceeds a threshold
*E* (i.e.
*P(effect difference* > 0%) ≥
*E*). When the trial stops for efficacy, the arm with the higher mean posterior distribution of the outcome proportion will be declared superior. Conversely, the trial will stop for futility if the two arms have equal or similar performance. The stopping rule for futility will be triggered if there is at least
*F*% posterior probability that the effect difference between the two arms is smaller than
*D* (
*P(effect difference* <
*D* %) ≥
*F*), where
*D* represents the maximum meaningful difference between the arms considered negligible, and F is the futility threshold for determining if sufficient evidence has been accrued
^
5,
6
^ (
Figure 1).

**Figure 1. f1:**
[figure not shown]
Decision-making processes of the trial. Interim analyses will be conducted every 7 days. At each analysis, all accumulated data will be evaluated according to two stopping rules: (
**a**) the stopping rule for efficacy, and (
**b**) the stopping rule for equivalence. If the intervention demonstrates clear superiority over the control, the trial will terminate and adopt the intervention arm. Conversely, if the control arm shows clear superiority over the intervention, the trial will stop and adopt the control arm. If the two arms show equivalent performance, the trial will stop and adopt the control arm. If neither stopping rule is met within one year of trial initiation, the trial will conclude and adopt the control arm.

Simulations were conducted to determine the decision thresholds
*E*,
*F*, and
*D* within optimal bounds, ensuring both adequate power and feasible sample sizes for the VIP programme. The simulations used datasets with small effect differences ranging from 0% to 5%, to configure thresholds for detecting small intervention effects. Various decision thresholds were tested, evaluating their impacts on performance measures including type I error, power, sample size, coverage, and bias.

Concurrently, the programme team discussed the level of evidence required to make decisions on the effectiveness of the intervention. This study is classified as a negligible risk trial with low-risk service modifications aimed at improving access to care. The team was willing to accept some chance of implementing the intervention if the two arms were equally effective. They also acknowledged a potentially small chance of adopting a marginally inferior arm, in order to prioritize a higher likelihood of adopting the intervention if it was indeed effective and to expedite the decision-making process within the trial.

Based on the simulation results and discussions, it was concluded that setting
*E*=95%,
*F*=95%, and
*D*=1% provided sufficiently high power while maintaining manageable sample sizes for the VIP programme. Consequently, this trial will employ the following two stopping rules for the primary outcome:

(a)The trial will stop if there is evidence of efficacy, defined as any meaningful difference greater than 0% between the two arms. If the posterior probability of observing a difference meets or exceeds 95%, the arm with the higher mean posterior distribution of outcome proportion will be declared superior, prompting the trial to stop.(b)Alternatively, the trial will stop if the difference between the two arms is negligible, defined as less than 1%. If there is at least 95% posterior probability that the difference is smaller than 1%, the trial will stop for futility, recognizing both arms as viable options.

Simulations using these stopping rules provided probabilities of adopting the intervention under different scenarios. The results indicate an 81.0% chance (power) of adopting the intervention if it increases attendance by 1%, with a median sample size of 3,800 (IQR [700-14,600]) required to achieve these results. If the intervention increases attendance by 3%, it will be correctly identified 94.3% of the time, with a median sample size of 1,300 (IQR [500-3,300]). In cases where there is no true difference between the two arms, the intervention would be adopted 36.3% of the time (type I error). If the intervention decreased attendance by 1% compared to the control arm, there is a 9.3% risk the intervention would be adopted.

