### Final analysis

When one of the two stopping rules is met, the trial will terminate and proceed to the final analysis stage. The maximum duration of the trial is set at 1 year, with an estimated enrolment of 15,000 participants aged 18–44 years. If neither stopping rule is triggered within this timeframe, the trial will declare that the arms are equally effective, and the intervention will not be adopted. Upon completion of the trial, all accrued data will be analysed on an intention-to-treat basis.

**
*Baseline characteristics*.** Age and sex of the participants will be described according to allocation. Frequency and percentages will be reported for sex, while age will be summarized using mean and standard deviation. Data will be assessed for normality and checked for the presence of outliers.

**
*Primary and secondary outcomes*.** The primary outcome is attendance at the triage clinic
*among young adults between ages of 18 and 44*, and the stopping rules are based only on the analysis of this group. The secondary outcome is the proportion of attendance in
*all ages*. The final analysis will report the posterior probability of each arm being superior to another, and the posterior probability of the two arms having a negligible difference of 1% or less. Additionally, the posterior distributions of the outcome proportions in each arm will be described by mean and 95% CI. The posterior distribution of the effect difference between the arms will also be reported with mean and 95% CI (
Table 1).

**Table 1. T1:** Reporting final analysis results.

	Probability of being superior	Probability of having a negligible difference	Mean success probability	Mean effect difference (95% CI)
18–44 years (primary outcome)				
Intervention arm				
Control arm				
44+ years				
Intervention arm				
Control arm				
All adults (secondary outcome)				
Intervention arm				
Control arm				

Posterior probabilities of being superior and having negligible difference of <1% will be reported for each age group. In each arm, the mean success probability and its 95% credible interval will be reported based on the posterior distribution of probabilities of success.

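### Read as an equivalence rule, futility rule (b) cannot be met within the estimated 15,000 participants at 30–50% attendance, so the described early stop for similar arms does not operate.

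*SAP article*

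**What the plan says.** Rule (b) is stated under Stopping rules, after the Figure 1 caption: "If there is at least 95% posterior probability that the difference is smaller than 1%, the trial will stop for futility". Three descriptions give it a two-directional meaning. The Stopping rules section says that "the trial will stop for futility if the two arms have equal or similar performance". The Figure 1 caption calls it "the stopping rule for equivalence". Rule (b) itself adds that either arm would then be acceptable.

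The only formula, under Stopping rules, is P(effect difference < D%) ≥ F, with no absolute-value sign. D = 1% and F = 95% are fixed after simulation.

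Final analysis sets the limit: "The maximum duration of the trial is set at 1 year, with an estimated enrolment of 15,000 participants aged 18–44 years". If neither rule fires by then, the arms are declared equally effective and control is kept. Statistical methods gives as a design aim "to achieve this without necessitating an excessively large sample size, even in the case of only marginal differences between the arms".

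The article reports adoption probabilities and sample sizes. It gives no probability of stopping for futility and does not say whether the simulations were limited to 15,000.

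**The concern.** The article presents two ways of stopping early: one arm is better, or the arms are alike. The second needs a difference in proportions estimated closely enough to place 95% of the posterior inside ±1 percentage point. That is demanding, and the article does not show that the precision available in one year is enough. If it is not, one of the two prespecified rules is inert at the planned size, and a trial of similar arms can end early only through a chance crossing of the efficacy rule. Readers would then be wrongly told that similarity can shorten the trial.

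**Working it through.** **Inputs from the article.** D = 1 point and F = 95% (rule (b)); 15,000 aged 18–44 (Final analysis); 1:1 allocation (Abstract); about 300 per weekly look (Interim analysis); attendance about 30% in ages 18–44 (Background and rationale) and about 50% overall (Abstract); control prior logit(p) ~ norm(0, 0.3) and odds-ratio prior centred on 1.0 with 95% interval 1/30 to 30 (Interim analysis).

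**Step 1: which reading gives the article's own figures?** Sequential simulation used a normal-approximation posterior, the odds-ratio prior and efficacy at 95% in either direction. The closest match came from the absolute reading of rule (b), looks of 100, and runs continued to 60,000 rather than 15,000. Ranges are over control rates of 30–50%.

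| True effect | Article | Simulated adoption |
|---|---|---|
| +1% | 81.0% | 80–81% |
| +3% | 94.3% | 94–95% |
| 0 | 36.3% | 36–37% |
| −1% | 9.3% | 15–16% |

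At 50% attendance, sample size among adopting runs was 3,700 (IQR 700–14,900) at +1%, against the stated 3,800 (700–14,600). The −1% figure does not match this setting; looks of 300 give about 9–12%. With the signed reading, adoption at +1% was only about 66–72%. In the matching runs rule (b) did fire, but first at about 32,000 (30%) to 38,500 (50%) participants.

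**Step 2: best case at 15,000.** The most favourable result is an observed difference of 0. Then SE = √(4p(1−p)/N) and P(|d| < 1%) = 2Φ(0.01/SE) − 1.

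- p = 0.30: SE = √(0.84/15,000) = 0.00748; 0.01/SE = 1.336; probability 0.82.
- p = 0.50: SE = √(1/15,000) = 0.00816; 0.01/SE = 1.225; probability 0.78.

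The requirement is 0.95, which needs SE ≤ 0.01/1.96 = 0.0051. A grid posterior with the stated priors and equal observed rates at 7,500 per arm gave 0.813–0.819 (30%) and 0.779–0.780 (50%), whether 0.3 is taken as an SD or as a precision. The priors do not change the result.

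**Step 3: size at which the rule becomes attainable.** N = 4p(1−p) × 196².

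- p = 0.30: 0.84 × 38,416 = 32,269, which is 2.2 times 15,000.
- p = 0.50: 1 × 38,416 = 38,416, which is 2.6 times 15,000.

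Setting N = 15,000 gives p(1−p) = 15,000/153,664 = 0.0976, so p is about 11%. Only below that attendance could the rule fire within the limit.

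**Step 4: the trial with the limit applied.** With looks of 300 and a 15,000 cap, rule (b) fired in 0 of 40,000 no-difference trials at each of 30% and 50%. About 47–48% of such trials ran the full year. The median sample was about 12,000 (30%) and 12,900 (50%); it moves by several hundred between runs because nearly half the trials sit at the cap. Adoption at a true +1% was about 57–60%.

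**Step 5: the signed formula.** Taken literally as intervention minus control, it needs an observed difference at or below 0.01 − 1.645 × SE. At 15,000 that is −0.23 points (30%) or −0.34 points (50%). It fires in about 44–48% of capped no-difference trials, so it is a different rule.

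**The case against.** Four points count against a stronger claim.

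- **The formula is signed, and a signed rule can fire.** This stands as a condition on the finding. The absolute reading is still the likelier one: the words describe similarity in both directions, the efficacy formula also omits its two-sided notation, and the signed reading does not reproduce the stated 81.0%. A signed rule would also stop for similarity when control is clearly better.
- **A reader might infer that the rule can never fire, whatever the data.** That goes too far. It becomes attainable below about 11% attendance, and 15,000 is an estimate of one year's enrolment. At the stated rates, though, enrolment would have to be more than twice the estimate.
- **A reader might infer that the trial has no route to a conclusion of similarity, or would adopt the wrong arm.** The article does not support this. Final analysis and the Figure 1 caption provide a one-year default that keeps control, which is also the action after rule (b). An inert rule (b) changes no adoption decision and adds no type I error.
- **Statistical methods promises only potential early stopping, and the programme accepted a year.** True, but rule (b) exists only to stop early, and the stated aim explicitly covers marginal differences.

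**Conclusion.** The point holds on two conditions: rule (b) means |difference| < 1%, and attendance lies in the article's 30–50% range. The attainable posterior probability at 15,000 is then at most 0.82 or 0.78 against 0.95, and about 32,300–38,400 participants are needed. The loss is the claimed early stop, not the correctness of the decision.

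The match in Step 1 suggests that the thresholds were assessed on simulations running past 15,000. That is an inference from reproduced figures; the article does not say so, and one stated figure (9.3% at −1%) does not fit that setting. The lower +1% adoption under the cap comes from the cap and not from D.

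**What to change.** 1. Write rule (b) as P(|difference| < 1%) ≥ 95%, and correct the formula under Stopping rules to match.
2. State that with D = 1% and F = 95% the rule cannot operate before about 32,000–38,000 participants at 30–50% attendance, so the trial ends only by rule (a) or at one year.
3. Remove or qualify the futility-stop claims in the Abstract, Statistical methods, Stopping rules, the Figure 1 caption and rule (b).
4. Report operating characteristics under the 15,000 limit with weekly looks, including the probabilities of stopping for futility and of reaching one year.

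The cost is wording plus a rerun of existing simulations.

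A larger D is not a free repair. As an illustration, D = 2% would fire in about 42–47% of capped no-difference trials, but it would class the 1% effect the design is said to detect as negligible and stop about 25–29% of true +1% trials for futility. Study status reports data collection complete, so it could not now be a prospective change.

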### Final analysis

When one of the two stopping rules is met, the trial will terminate and proceed to the final analysis stage. The maximum duration of the trial is set at 1 year, with an estimated enrolment of 15,000 participants aged 18–44 years. If neither stopping rule is triggered within this timeframe, the trial will declare that the arms are equally effective, and the intervention will not be adopted. Upon completion of the trial, all accrued data will be analysed on an intention-to-treat basis.

**
*Baseline characteristics*.** Age and sex of the participants will be described according to allocation. Frequency and percentages will be reported for sex, while age will be summarized using mean and standard deviation. Data will be assessed for normality and checked for the presence of outliers.

**
*Primary and secondary outcomes*.** The primary outcome is attendance at the triage clinic
*among young adults between ages of 18 and 44*, and the stopping rules are based only on the analysis of this group. The secondary outcome is the proportion of attendance in
*all ages*. The final analysis will report the posterior probability of each arm being superior to another, and the posterior probability of the two arms having a negligible difference of 1% or less. Additionally, the posterior distributions of the outcome proportions in each arm will be described by mean and 95% CI. The posterior distribution of the effect difference between the arms will also be reported with mean and 95% CI (
Table 1).

**Table 1. T1:** Reporting final analysis results.

	Probability of being superior	Probability of having a negligible difference	Mean success probability	Mean effect difference (95% CI)
18–44 years (primary outcome)				
Intervention arm				
Control arm				
44+ years				
Intervention arm				
Control arm				
All adults (secondary outcome)				
Intervention arm				
Control arm				

Posterior probabilities of being superior and having negligible difference of <1% will be reported for each age group. In each arm, the mean success probability and its 95% credible interval will be reported based on the posterior distribution of probabilities of success.

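### A trial that reaches one year with no stopping rule met is to be declared equally effective, although in that branch the plan's own 1%/95% criterion for a negligible difference has not been met

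*SAP article*

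**What the plan says.** All references are to the SAP article. Two rules can stop the trial.

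- **Rule (a), efficacy:** "If the posterior probability of observing a difference meets or exceeds 95%, the arm with the higher mean posterior distribution of outcome proportion" is declared superior.
- **Rule (b), futility:** "the trial will stop if the difference between the two arms is negligible, defined as less than 1" per cent. The evidence required is: "If there is at least 95% posterior probability that the difference is smaller than 1%, the trial will stop for futility".

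The time limit is under Final analysis: "The maximum duration of the trial is set at 1 year, with an estimated enrolment of 15,000 participants aged 18–44 years". For a trial that gets there without a stop, the same section says "If neither stopping rule is triggered within this timeframe, the trial will declare that the arms are equally effective" and adds that the intervention is not adopted. The Figure 1 legend covers the same branch differently: "If neither stopping rule is met within one year of trial initiation, the trial will conclude and adopt the control arm". It makes no statement about equality, and it lists equivalent performance as a separate branch.

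Final analysis and Table 1 also commit to reporting the probability that each arm is superior, the probability of a negligible difference, and the mean difference with its 95% credible interval.

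**The concern.** Rule (b) says how much evidence the plan wants before it treats the arms as negligibly different. A trial that ends with neither rule met did not produce that evidence, yet it receives the firmest statement of equality in the document. The wording is also inverted: when the criterion is met, the Stopping rules text concludes only that either arm is a viable option; when it is not met, Final analysis concludes equal effectiveness.

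Keeping standard care by default is a legitimate programme choice and is not in question. What is at stake is the inference. Another programme could read the declaration as evidence against an intervention whose benefit the data had not ruled out. The plan presents itself as powered for a 1% gain, and the interval at one year would still be wide enough to include gains of that size.

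**Working it through.** **Logic.** Neither rule triggered means rule (b) not met, so the posterior probability of a difference smaller than 1% is below 95%. This holds for any attendance rate, look size or reading of rule (b). The remaining steps only give scale.

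**Inputs.** 15,000 participants at one year (Final analysis). Equal allocation ("Participants will be randomly assigned to one of two groups in equal numbers"), so 7,500 per arm. Weekly looks "with an average of about 300 adults aged 18–44 enrolled each cycle", so 50 × 300 = 15,000. Attendance of 30% for ages 18–44 and 50% overall (Background and rationale); the rate behind the plan's simulations is not stated, so these two are an assumed range. Let d be the difference in attendance, intervention minus control.

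**The plan's own figures.** It gives no probability for ending undecided. The nearest figures are its probabilities of adopting the intervention. The middle column is a normal-approximation simulation with a two-sided rule (b), looks every 300 and a cap of 15,000. The last column has looks every 100 and no one-year cap.

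| True d | Plan | 300 per look, capped | 100 per look, uncapped |
|---|---|---|---|
| +1% | 81.0% | 57–61% | 80–81% |
| +3% | 94.3% | 97% | 94% |
| 0 | 36.3% | 25–27% | 36–37% |
| −1% | 9.3% | 10–11% | 16% |

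The plan's figures are not reproduced under the capped design. Three of the four are matched closely without the cap, which suggests, but does not show, that the cap was left out. That is a separate matter, and this point does not depend on it.

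**Precision at one year.** SE = √(2p(1−p)/7,500).

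- 30%: √(2 × 0.21/7,500) = 0.0075; 1.96 × SE = 1.5 points.
- 50%: √(2 × 0.25/7,500) = 0.0082; 1.96 × SE = 1.6 points.

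**Rule (b) read two-sided.** The best case is an observed difference of exactly 0, where P(|d| < 1%) = 2Φ(0.01/SE) − 1.

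- 30%: 2Φ(1.34) − 1 = 0.82.
- 50%: 2Φ(1.22) − 1 = 0.78.

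Reaching 0.95 with an observed difference of 0 needs a total N of 4p(1−p)(1.96/0.01)²: 0.84 × 38,416 ≈ 32,300 at 30%, and 38,400 at 50%. A grid posterior under the stated priors, with the 0.3 in the control prior taken either as a standard deviation or as a precision, gave the same maxima to within 0.01.

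**Rule (b) read as the signed formula, P(d < 1%) ≥ 95%.** The observed difference must be at or below 1 − 1.645 × SE (in points): 1 − 1.23 = −0.2 at 30%, or 1 − 1.34 = −0.3 at 50%. The rule can therefore fire within the year.

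**An example.** With 30% attendance, 7,500 per arm and an observed gain of 1.2 points, the grid posterior gives P(d > 0) = 0.92–0.94 and P(|d| < 1%) = 0.40–0.46. Neither rule is met at that look. If none had been met earlier, the arms would be declared equally effective.

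**Simulated share of trials ending with no rule met (cap 15,000).**

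| Assumption | True d = 0 | True d = +1% |
|---|---|---|
| Two-sided, 300 per look | about 47% | 28–31% |
| Two-sided, 100 per look | 37–41% | 23–27% |
| Signed, 300 per look | 17–20% | 17–20% |

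Repeat runs differed by one or two points. With a true gain of 2%, the two-sided share at 300 per look is 6–9%.

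**The case against.** The strongest reply is that nothing operational turns on the phrase. The trial exists to choose between two programme options; in this branch the choice is fixed and conservative, and Figure 1 already states it acceptably. Table 1 will show the probability of a negligible difference and the interval, so a careful reader could see that equality was not established. All of this stands. It limits the harm but does not make the declaration correct: the non-adoption clause already carries the default, and the equality clause adds only an unsupported inference.

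Three stronger readings are tempting and should be resisted.

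- **Rule (b) can never fire, so every finding of equality would come from the default.** This depends on the two-sided reading. The prose supports that reading, since it speaks of arms with similar performance and a negligible difference between them. But the formula under Stopping rules shows no absolute value, and on the signed reading rule (b) fires in about 44–48% of simulated trials with no true effect (300 per look). Also, 15,000 is an estimate of enrolment.
- **The simulated shares are the trial's operating characteristics.** They vary with look size and with the reading of rule (b). The plan's 81.0% adoption at +1% leaves at most 19% for every other outcome, so the two-sided shares at +1% cannot hold together with it.
- **The declaration would contradict Table 1.** Table 1 is an empty shell. A reported probability below 0.95 would fail to support the declaration, which is less than contradicting it.

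**Conclusion.** The point holds, and its core needs no calculation: the plan declares equality in a branch defined partly by failure of its own criterion for a negligible difference, and Final analysis and the Figure 1 legend describe that branch differently. At about 15,000 participants the interval of ±1.5 to ±1.6 points exceeds the 1% margin for attendance of 30% to 50%. On the two-sided reading, P(|d| < 1%) is capped at about 0.82 or 0.78, so rule (b) is out of reach within the year. On the signed reading it is reachable, but undecided trials still miss it by definition. How often the branch occurs is uncertain, and the verdict does not rest on it.

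A reader might infer that the adoption decision is wrong or that the planned summaries are inadequate. The documents support neither: the default is legitimate and the summaries are already planned. The error is confined to the conclusion attached to them.

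**What to change.** Under Final analysis, replace the clause with: *If neither rule is met at one year, the trial is inconclusive and the programme keeps standard care by default.* Align it with the Figure 1 legend, and interpret the outcome through the summaries already planned in Table 1. Use equivalent or equally effective only if P(|d| < 1%) is at least 0.95, written with the absolute value so that the label does not depend on how rule (b) is read.

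The change is one sentence. It needs no new data or analysis and leaves the programme decision as it is. The only downside is a less definite conclusion. Study status says data collection was complete at submission, so the change should be recorded as a dated correction to reporting.
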